### Sample

The sample of 50 volunteers was calculated assuming a 40% difference in the proportion between the active TDCS and placebo groups in performance before and after the interventions. This calculation was performed using an online statistical program, considering an alpha of .05 and a power of 0.80, resulting in a sample of 25 individuals in each group (intervention and control). To approximate unexpected factors, we applied a 20% dropout rate, reaching a total sample size of 60 individuals.

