### Assessments

Once eligibility and consent have been approved and completed, volunteers will undergo the Stroop test (based on the study by Campanholo et al [17]). This test consists of two tasks, one for reading and the other for naming the color. In both, the stimuli are color names printed in incongruous colors. The word-reading task gives an indication of reading fluency and serves to establish a benchmark for performance effectiveness relative to the color-naming task. The fact that there is an incongruity between the word name and the ink color causes an interference effect in the color naming. This interference is the Stroop color effect. Tests inspired by the Stroop effect are widely used in neuropsychology to measure individuals’ executive control and concentration [17].

After performing the Stroop test, the participant will undergo an assessment of cerebral blood flow by means of a transcranial Doppler ultrasound examination of the middle cerebral artery. The protocol developed by Rogge et al [18] will be carried out. Color-coded transcranial Doppler ultrasound will be performed in combined color and power mode with an ultrasound system equipped with a 2.5 mHz multifrequency probe transducer. Transtemporal insonation will be performed through the temporal bone window using axial and axial insonation plans and coronal with the participant in the right dorsal decubitus position. No eco-enhancer contrast will be used. Peak systolic and end diastolic pressure velocities will be measured in pulsed wave mode. Flow velocity measurements will be performed without angle correction. The examiner was free to optimize the images by changing the pulse gain and repetition frequencies [18].

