### Statistical Analysis

For the sociodemographic and epidemiological description of the groups, we will use the usual procedures of descriptive statistics such as calculation of frequencies and measures of central tendency and dispersion. The Shapiro-Wilk test will be performed to assess the assumption of normality of the outcome variables.

For analysis of paired and independent samples using a *t* test for comparisons within and between intervention groups or applying equivalent nonparametric tests (according to the results of the Shapiro-Wilk test) before and after the intervention, *P* values <.05 will be considered significant. Data will be organized and tabulated using SPSS (IBM Corp).

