### Outcome Variables

The guiding theme of this study is to use tools or strategies to improve learning and promote better retention. The primary expected result is a greater correctness of answers in two phases of the Stroop test (word reading and color recognition) and a decrease in test execution time.

Secondary variables are based on physiological responses of cerebral blood flow where we expect to find an increase in velocity and systolic and diastolic peaks. This hypothesis is based on functional magnetic resonance studies where the results show an increase in local blood flow after the use of TDCS.

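### The primary outcome is three or four Stroop measures, each judged at P<.05 with no stated success rule, so the design's 5% error and 0.80 power cannot both be relied on

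*Protocol article*

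**What the plan says.** Outcome Variables (protocol article): the primary expectation is more correct answers in two Stroop phases together with a faster test, given as "word reading and color recognition) and a decrease in test execution time". The section does not say whether time is one total or one value per phase.

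Statistical Analysis: outcomes are examined "using a *t* test for comparisons within and between intervention groups or applying equivalent nonparametric tests", before and after the intervention, and *P* "values <.05 will be considered significant". No measure and no comparison is marked as the decisive one.

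Sample: the trial is sized on a single 40% difference in a proportion, "considering an alpha of .05 and a power of 0.80, resulting in a sample of 25 individuals in each group". The Stroop measure behind that proportion is not named.

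Assessments: word reading indicates reading fluency and "serves to establish a benchmark for performance effectiveness relative to the color-naming task". The outcome definition gives both tasks equal standing.

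**The concern.** A 5% error rate and 0.80 power describe one test of one quantity. Here the primary result has three or four components, and the shown text does not say how they combine into a verdict. Two rules are possible, and neither delivers both design figures:

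- **Any one suffices.** There are three or four chances of a primary claim at .05, so the overall error exceeds 5%.
- **All are required.** The error is controlled, but the chance that every component succeeds is lower than the chance for any one of them.

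With the rule open, it could be settled after the results are known. The within-group tests at the same threshold add further routes to a significant primary finding. They are not comparisons of active with placebo stimulation.

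**Working it through.** **1. The plan's own figure.** Sample size for two proportions differing by 0.40, two-sided .05, power 0.80 (the article gives neither the baseline nor the sidedness, so both are assumed):

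n per arm = [1.960·√(2p̄(1−p̄)) + 0.8416·√(p₁(1−p₁)+p₂(1−p₂))]² / 0.40²

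For an assumed 0.30 vs 0.70: (1.960×0.7071 + 0.8416×0.6481)² / 0.16 = (1.386 + 0.545)² / 0.16 = 23.3, so 24. With a continuity correction, 0.10 vs 0.50 gives 25. The stated 25 per arm is therefore reproducible, as the size for **one** test at .05.

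**2. Number of primary tests.** Correctness in word reading, correctness in color naming and execution time make k = 3. Time per phase makes k = 4. Only one between-arm test per measure is counted.

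**3. Any one suffices.** If independent, error = 1 − 0.95^k:
- k = 3: 1 − 0.857 = 14.3%
- k = 4: 1 − 0.815 = 18.5%

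For correlated measures, equicorrelated normal test statistics were simulated (1,000,000 draws, two-sided .05 each). The article gives no correlations, so a range is shown:

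| Assumed correlation | k = 3 | k = 4 |
|---|---|---|
| 0 | 14.3% | 18.5% |
| 0.5 | 12.5% | 15.6% |
| 0.7 | 10.9% | 13.0% |
| 0.9 | 8.4% | 9.4% |

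**4. All are required.** The error cannot exceed 5%. With no effect on any measure, it is 0.01% for three independent measures, 0.9% at correlation 0.7 and 2.2% at 0.9. Joint power, if each measure has 0.80:
- k = 3, independent: 0.80³ = 51%
- k = 3, correlation 0.5 (simulated): 61%
- k = 4, independent: 0.80⁴ = 41%

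**5. Effect of a correction.** A Bonferroni split, which is Holm's first step, uses .05/3 = .0167 or .05/4 = .0125. The familywise error is then 4.9% if independent. For the assumed 0.30 vs 0.70 with 25 per arm, power per measure falls from 83% to 68% (k = 3) or 64% (k = 4). The n per arm for 0.80 rises from 24 to 32 or 34. Holm rejects at least as often as Bonferroni, so these losses are upper bounds.

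**The case against.** The strongest reply is that the article never says one significant measure is enough. Outcome Variables joins the components with an 'and', which can be read as requiring all of them, and on that reading the error is below 5%. This stands, and it is why the inflation is stated only conditionally. It does not rescue the design, because the same reading gives up the stated power.

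A success rule or multiplicity procedure could also sit in an analysis plan that is not shown. That is fair, so the absence of a rule is claimed only for the shown text. The multi-part primary definition and the general .05 threshold are the article's own.

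The expected results are directional. Counting only false positives in the predicted direction, three independent two-sided tests give 1 − 0.975³ = 7.3% and four give 1 − 0.975⁴ = 9.6%. The matching figure for a single test is 2.5%, so the inflation remains.

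A reader might infer three stronger points that the document does not support:

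- **That interference is the trial's intended effect, so improved word reading cannot count.** Assessments describes how the Stroop test works. It does not call interference this trial's endpoint. It calls word reading a benchmark, but not solely a benchmark.
- **That retest practice would create a false success.** Both randomized arms follow the same Stroop schedule, so practice should largely cancel between them. It threatens only the within-group tests.
- **That the primary must become color-naming time minus word-reading time.** That is a preference. It cannot be computed if only total time is recorded, and the sample size calculation gives no basis for it.

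**Conclusion.** The point holds in conditional form. The primary result consists of three or four Stroop measures, tested at .05 throughout, with no named primary comparison and no success rule in the shown text. If any one between-arm test suffices, the error is about 11% to 18.5% for assumed correlations from 0.7 down to 0, and 8% to 9% at 0.9. If all are required, joint power for three measures is about 51% to 61% for assumed correlations of 0 to 0.5, with each measure at 0.80. It would be wrong to say flatly that the trial's error rate is 11% to 18.5%: that needs both the any-one rule and a correlation of about 0.7 or less, and the article states neither. Under either rule, the stated .05 and 0.80 would hold together only if the measures were almost perfectly correlated.

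**What to change.** Before primary data are seen, do one of the following:

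- **One primary (simplest).** Name one existing Stroop measure, compared between arms at the final assessment, as the sole primary at two-sided .05, and make the others secondary. Color naming is the natural candidate, because Assessments describes word reading as its benchmark. The interference contrast is an option only if time is recorded per phase, and it would need its own sample size basis.
- **Keep all measures.** List them, say whether time is total or per phase, and apply Holm to the between-arm tests.

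In both cases, treat within-group tests as descriptive and restate power for the chosen rule and measure.

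The cost is wording in the protocol and registry, with no new data for an existing measure. Under the first option, the other measures can no longer carry a primary claim at unadjusted .05. Under Holm, power is somewhat lower. The Results section says enrollment has begun and secondary-outcome analysis is under way, so the change should be dated and made promptly.

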## Results

The trial and enrollment began in July 2022. The statistical analysis for the secondary outcomes are currently being performed.

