**Results:**

Participants will be recruited between July 2022 and December 2022. This study is expected to conclude in July 2023.

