## Methods

### Study Design

This is a prospective, parallel, double-blind, randomized controlled, and 2-armed clinical trial. This study will be single center and carried out on the premises of Faculdade São Leopoldo Mandic/Campinas, São Paulo, Brazil.

After an initial evaluation carried out by a research collaborator (collaborator 1), the participant will carry out the research protocol with another collaborator (collaborator 2) according to the draw performed by this collaborator. At the end of the protocol, the participant will again undergo an evaluation that will be performed by collaborator 1. Only collaborator 2 will know if the participant performed active stimulation or placebo. Therefore, this procedure will allow blinding of the participant and collaborator 1 (evaluator) to the stimulation conditions (Figure 1).

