### Randomization and Blinding

Once eligibility and consent have been approved and completed, randomization will occur using the random list generated by an automated web-based randomization program. Participants will be randomly assigned into 1 of the following 2 groups:

Group A: TDCS active + neurofeedbackGroup B: placebo TDCS + neurofeedback

Participants randomized to receive placebo TDCS will have the opportunity to enroll in an open-label portion of the study upon completion of their participation in the randomized portion of the study.

This process will be carried out by a member of the research team (collaborator 3) who is not involved in the study recruitment or development process.

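### The placebo-only open-label offer reveals arms one by one while the trial is still running, and the article reports an unexplained secondary-outcome analysis during recruitment

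*Protocol article*

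**What the plan says.** **Disclosure of arm.** Study Design describes a single-centre, double-blind trial. Collaborator 1 evaluates before and after, collaborator 2 delivers the protocol, and "Only collaborator 2 will know if the participant performed active stimulation or placebo". Under Randomization and Blinding, those allocated to placebo "will have the opportunity to enroll in an open-label portion of the study upon completion of their participation in the randomized portion". No such offer is described for the active arm.

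**Timing.** The Abstract says "Participants will be recruited between July 2022 and December 2022" and "This study is expected to conclude in July 2023". The main Results section says "The trial and enrollment began in July 2022" and then "The statistical analysis for the secondary outcomes are currently being performed". The article is dated 26 August 2022. Outcome Variables identifies what is being analysed: "Secondary variables are based on physiological responses of cerebral blood flow", that is, the transcranial Doppler measures. Statistical Analysis gives within-group and between-group tests at P<.05 and describes no interim look.

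**The concern.** **The open-label offer.** An offer made only to one arm tells each recipient their allocation. It also tells a finisher who receives no offer that they had active stimulation, and it tells any staff member who handles or hears of it. Because it follows each person's own completion, this happens throughout accrual. Participants are medicine and dentistry undergraduates of one institution, so those who have finished are likely to know some who have not. The sham works by sensation: an initial itch, then no current. Someone who has knowingly had both sham and active stimulation can describe the difference to a classmate. The primary outcome is Stroop accuracy and execution time, which depends on effort and is open to expectation. If collaborator 1 learned the arms of finishers, the evaluator's blinding would weaken as well.

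**The reported analysis.** The text places an outcome analysis inside the recruitment window. If it compared arms, it could influence conduct and later analysis choices, and a second test at the end would raise the false-positive rate for that outcome. The article does not let a reader tell whether that happened.

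**Working it through.** **1. The two blinding statements side by side.** Study Design limits knowledge of the arm to collaborator 2. Randomization and Blinding requires each placebo participant to be identified as such on finishing. From then on at least that participant also knows, and participants who receive no offer can infer theirs. The two statements agree only if the first applies no further than each person's own treatment and evaluation, and the article does not say so.

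**2. Whose outcome is exposed.** Study Design puts collaborator 1's second evaluation at the end of the protocol. The offer comes on completion, so the finisher's own outcome is already recorded. The exposure is to participants still in treatment or not yet enrolled.

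**3. How many that is.** Inputs: 60 participants (Sample); 10 sessions over two weeks with a 2-day gap (Transcranial Direct Current Stimulation), so 5 + 2 + 5 = 12 days; recruitment from July to 31 December 2022. Assumption: even accrual. A start on 1 July gives 184 days and a start on 31 July gives 154.
- Not yet enrolled when the first participant finishes: 60 × (184 − 12)/184 = 56.1, or 60 × (154 − 12)/154 = 55.3.
- Placebo participants finishing while accrual is open, with 30 per arm and no dropout: 30 × 172/184 = 28.0, or 30 × 142/154 = 27.7. If 20% of the 30 drop out, 24 finish, giving 24 × 172/184 = 22.4 or 24 × 142/154 = 22.1.

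These count opportunities for disclosure, not known breaches.

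**4. When the reported analysis took place.** The statement was written no later than 26 August 2022, which is 56 days after 1 July or 26 days after 31 July.

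| Start | Enrolled by 26 August | Finished 12-day course | Share of 60 |
|---|---|---|---|
| 1 July | 60 × 56/184 = 18.3 | 60 × 44/184 = 14.3 | 23.9% |
| 31 July | 60 × 26/154 = 10.1 | 60 × 14/154 = 5.5 | 9.1% |

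So about 5 to 14 participants could have had a post-treatment Doppler measurement. These are upper limits, since the text was written before it was published.

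**5. Error rate if the look was by arm and repeated.** Let t be the information fraction at the look. Under no effect, the early and final statistics are standard normal with correlation √t. The chance of at least one false positive is P(|Z₁| > 1.96 or |Z₂| > 1.96).
- t = 0.24: 9.1%.
- t = 0.10: 9.5% (also 9.5% at t = 0.091).

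If the work was pooled or blinded, or was not used for inference, the rate stays at 5%.

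**The case against.** The strongest reply is that the Results sentence is probably loose drafting. The Abstract still puts recruitment in the future, and only a handful of participants could have finished. The sentence names no comparison by arm, no recipient and no result. That stands. A reader might infer that results were released, or that arms were compared early, but nothing in the article says so. Pooled work such as Doppler image processing or baseline description would do no harm. Nor can it be said that no interim analysis is planned, because the full protocol and analysis plan are not shown. It can only be said that the article describes none. Any error inflation would concern the secondary Doppler outcomes, not the Stroop test.

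On the open-label offer, it can fairly be said that collaborator 2, already unblinded, could make it without collaborator 1 knowing. The sham copies the initial sensation, and talk among students is a possibility rather than a documented event. These points limit the size of the risk. They do not remove the stated rule: the offer is tied to each person's own completion and goes to one arm only, and nothing says how arm is then kept from the evaluator.

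A reader might also infer that participants' own results are biased by the offer. They are not, because the final evaluation comes first. Nor can it be inferred that later allocations become predictable, since the article mentions no blocks.

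**Conclusion.** The point holds in two parts of unequal weight.

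The firmer part is the open-label rule. As written, it reveals arms person by person during accrual and conflicts with the statement that only collaborator 2 knows them. On even accrual, roughly 22 to 28 placebo participants would finish while recruitment is open, depending on dropout. The effect on blinding cannot be quantified from the document, but the weakness is avoidable at little cost.

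The second part is an unexplained statement that needs correction or disclosure. It places a secondary-outcome analysis at most 56 days into a recruitment that runs to December 2022. The 9.1–9.5% error figure depends on three things the article does not state: that arms were compared, that the test was at two-sided .05, and that it was repeated at the end. It also assumes even accrual. Without those, the rate is 5%.

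**What to change.** 1. Make the open-label offer, and any disclosure of arm, only after the last participant's final assessment and database lock. Keep allocation from collaborator 1 until then.
2. Reconcile Study Design with Randomization and Blinding on who knows the arm, when and by what route it is disclosed, and who handles allocation. The first section has collaborator 2 perform the draw; the second gives the process to collaborator 3.
3. State that no outcome is compared by arm before database lock.
4. Correct the Results sentence. If an analysis did take place, disclose what was analysed, whether it was by arm, and who saw it.

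The cost is protocol wording, plus a wait of some months for placebo participants who want the open-label phase. The sample size is unaffected.

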## Discussion

We believe that the resources used in this study can help improve some aspects of declarative memory, since learning and memory processes modify the brain. Strategies to enhance the acquisition, storage, and use of information must be able to sensitize (motivate) and involve volunteers in the learning process, thus clarifying their role.

The performance of a task depends on ongoing brain activity that can be influenced by attention, excitement, or motivation. Scientific studies confirm that mindfulness leads to better performance, health, and well-being. However, these factors that modulate cognitive efficiency are nonspecific, can be difficult to control, and are not suitable to specifically facilitate neural processing.

The first stages of memory consolidation involve the stabilization of structural and functional neural changes and other neural changes generated by learning. New methods of memory consolidation optimization are being suggested (authors) in the role of neuromodulation.

The human brain is a highly interconnected network with high information processing efficiency. This efficient processing network operates through specialized structures and functions [21]. Among the essential functions of humans, memory requires significant attention from researchers because it is the ability to store and evoke learned knowledge [2]. The storage and use of learned information in the brain are fundamental for the interaction and modulation of human behavior and the adaptation and interaction of individuals with their environment [22].

In recent years, there has been an increase in technological improvement and neuroscientific discoveries aimed at new forms of training focusing on increasing memory performance [23].

As already described, neurofeedback is a brainwave training technique used to improve performance in terms of creativity, attention, and memory [24]. It has also been used as a potential cognitive and behavioral adjuvant for healthy individuals [6,25]. However, the effectiveness of neurofeedback with healthy participants received criticism from the scientific community since most studies failed to provide evidence for changes in behavioral and electrophysiological measures, mainly due to methodological deficiencies such as the lack of a sham/control group [26]. In response to this lack of reliability, Wang and Hsieh [3] researched young and older adult individuals to investigate the effectiveness of the cortical activity training protocol on attention and working memory performance. The authors observed better performance in older adults, with a significant improvement in memory among the young [3].

Although recent discoveries are addressing and answering old and new questions, the current findings provide insights into the underlying mechanisms of neurofeedback training in cognitive function. Furthermore, the results indicate that an intervention program protocol could be effective against cognitive aging and memory decline [3].

The future of neurofeedback research lies primarily in mobile recording and real-time feedback of the emotional and cognitive states of the individuals being evaluated. Due to volume conduction (the ability to measure electrical potentials at a distance from their source generators), single channels, regardless of where they are placed on the scalp, can capture a substantial fraction of all brain dynamics. Indeed, Rebolledo-Mendez et al [25] used attention levels as an input to interface systems between the brain and a computer, and found that the device provides accurate readings regarding attention since there is a positive correlation between measured and self-reported attention levels. However, setbacks observed by the authors included difficulties using the device due to the size of the head, interference with the hair, and no indicator for low batteries [25].

The primary reason for selecting this equipment is that it is a single dry electrode system, a type of EEG that does not require any substance or solution between the skin and the electrode. This feature makes the testing process more agile and reduces the individual’s discomfort. Johnstone et al [27] reported that the results obtained with this type of EEG are comparable to other devices that use different sensors and conductive substances. Additionally, it is easy to use and access the data since the equipment communicates with a computer via Bluetooth, making analyses and treatment more efficient. Furthermore, this technology comes at a low cost. These characteristics facilitate research and allow acquisition by any individual without substantial training [27].

The other device suggested for applying this protocol uses TDCS. This technique has been shown to elicit lasting effects in different protocols and diseases. TDCS provided the beneficial effect of anodic direct current stimulation of increased excitability in simple reaction times and implicit motor learning when stimulating the primary motor cortex [28] and improved learning of a visual-motor coordination task by stimulating the primary motor area or the V5 visual area [29].

Regarding its action on working memory, Fregni et al [11] demonstrated that anodic stimulation in the left DLPFC improves working memory performance. This effect depends on the polarity of the stimulation and is specific to the stimulation site. The results of Fregni et al [11] were further corroborated by Javadi and Walsh [30], who performed two experiments involving 32 participants who performed a series of word memorization tasks. This task was performed during simulated anodic and cathodic stimulation to the left DLPFC. Participants in the first experiment performed the same task with anodic TDCS of the primary motor cortex (M1). The results indicated that active stimulation of the left DLPFC leads to an improvement or attenuation of verbal memorization depending on the polarity of the stimulation. For example, during encoding, anodic stimulation of the left DLPFC improved memory, while cathodic stimulation of the same area impaired memory performance in later recognition. Anodic stimulation of M1 did not affect later recognition [30]. Smirni et al [31] observed and confirmed the same results.

To date, we have not found scientific studies using the association of the two techniques. We believe that using neurofeedback in conjunction with TDCS can potentiate the effects of training and thus provide greater effectiveness and long-term effects on the memory of individuals. In the long term, we expect that our results might further comprehensive programs for these conditions.

